### 2.3. Intervention Condition

Family UNited will be delivered to families in groups of approximately 12 families. Only one or two parents or main caregivers will be invited to attend, with a maximum of two children under their care aged 8 to 15 years.

The programme consists of four meetings (Table 1) spread over four weeks. In the first hour of each week, two facilitators will work with caregivers in one room; whereas, the other two facilitators will work with the children in a separate room. In the second hour of the meeting, all four facilitators and all caregivers and children will come together in one room for the joint family session.

During the caregiver sessions, caregivers will learn about children’s behaviour and how caregiver attention changes children’s behaviour. They will learn techniques to make the behaviour they want to see more likely to happen. They will practice how to communicate with their children in a way that is healthy and promotes listening. They will also be shown ways to make sure their children know that they are loved and, at the same time, how to set limits that help the children stay safe and feel secure.

During the child sessions, children will learn about some good ways to deal with stress and the importance of talking to trusted adults about their feelings. They will think about their caregiver’s responsibilities and have discussions about the positive qualities they want to develop and use as adults. In addition, children will learn and practice ways to deal with peer pressure situations, increasing the likelihood that they will stay healthy and safe.

In the family sessions, caregivers and their children will come together to practice positive and respectful communication. Together, they will play games and participate in activities that encourage positive relationships and build trust. The children will enjoy one-to-one time with their caregivers while talking about the strengths and qualities they share as families and the things they can do together to demonstrate their family values.

Based on the process evaluation, we will monitor participants’ attendance at each of the sessions and calculate the “Reach” and “Dose received”, as shown in Table 2.

During the trial period, participants will be requested not to take part in any other family skills programme, nor will any other contacts be made with the families, apart from the scheduled sessions of the Family UNited programme.

Facilitators in both Trentino and Parma have been trained on Family UNited through 3 full-day in-person workshop in December 2021. They reached pilot families in March/April 2022 and implemented the programme. The same facilitators will implement Family UNited during the planned cRCT.

### 2.4. Waitlist/Control Condition

Participants allocated to the waitlist/control group will only receive the questionnaires at the same time as the families in the intervention group. They will not receive any family skills intervention, nor will any contact be made with facilitators before all data have been collected. Only then the waitlist/control families will start the Family UNited training programme, as shown in Figure 2.

### 2.5. Outcomes

The primary outcome of this trial is to assess the efficacy of Family UNited in improving family skills outcomes and family mental health by assessing caregivers’ parenting skills, parental confidence, and mental health, as well as their children’s behavioural and mental health outcomes, resilience capacities, and aggression and hostile behaviour as short-term impacts, as described in the logic model (Figure 1). To assess this, caregivers and children will complete a battery of questionnaires, right before the intervention (Time 1), two weeks post-intervention (Time 2), and six weeks post-intervention (Time 3); mean/median scores will be compared, as described in the data-collection and proposed-analysis sections.

In addition, semi-structured interviews will be conducted with a select group of caregivers that have completed the Family UNited programme and facilitators who will include experiences and recommendations through a qualitative perspective.

To calculate families’ rates of recruitment and attendance to the programme and to evaluate the fidelity and completeness of the programme delivery, we adapted the framework developed by Linnan and Steckler [23]. This framework includes seven key dimensions that need to be evaluated: context (environmental aspects of the intervention setting), reach (the proportion of participants who received the intervention), fidelity (whether the intervention is delivered as planned), dose delivered and received (the amount of intervention delivered and the extent to which participants responded to it), implementation, (a composite score of reach, dose, and fidelity), and recruitment (methods used to attract participants).

The framework has been previously used to evaluate the SFP 10–14 programme in the UK [24], as well as the Strong Families programme in Afghanistan [8] and Iran [10]. A template of the indicators is shown in Table 2. Observers (independent research assistants) will attend all Family UNited programme sessions, track family attendance for every session, and provide external evaluation feedback based on standardised questionnaires, which have been used previously [8,10]. Facilitators will likewise complete internal evaluation forms, out of which the indicators, as shown in Table 2, will be calculated. To identify key factors influencing attendance and adherence, we will conduct interviews with caregivers, facilitators, researchers, and coordinators; whereas, our tertiary objective, exploring the cultural acceptability of the programme by families, will be assessed through interviews with caregivers.

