### 1.4. Objectives of This Study

The current study aims to explore the efficacy, fidelity, and acceptability of this universal prevention programme with families in Trentino and Parma, Italy and investigate the feasibility of delivering the programme.

The primary objective (impact evaluation) will be to test the efficacy of the Family UNited programme in improving family-skills outcomes and caregiver and child mental health and resilience, as reported by caregivers and children, when implemented in Trentino and Parma, Italy. According to the logic model of Family UNited (Figure 1), the short-term participant and family impact will be measured and compared against a waitlist/control group.

The secondary objective (process evaluation) will be to calculate the extent of families’ attendance to Family UNited sessions to evaluate the completeness of programme delivery. Further, the fidelity will be assessed to ensure facilitator compliance with the programme, as trained.

The tertiary objective will be to explore the cultural and contextual acceptability of the Family UNited programme for families in Trentino and Parma, Italy.

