### 2.10. Data Collection Methods

All participating caregivers and children will complete a battery of measures at three points; one week pre-intervention (t1), two weeks post-intervention (t2), and six weeks post-intervention (t3), either electronically through Google Forms or conventionally through paper-based forms, as shown in Figure 3. At baseline, the Family Demographics Questionnaire (FDQ) will provide information on the age and gender of the caregivers, their marital, educational and work status, and the number of children they care for under the age of 16 years. In addition, caregivers will provide information on the age and gender of their children and their relationship to them. They will further provide information on their country of origin (if not Italy) and how long they have been living in Italy.

The Strengths and Difficulties Questionnaire (SDQ) is a 25-item behavioural screening questionnaire through which we intend to measure potential changes in children related to short-term impacts, such as “Improved child behaviour”, “Reduced aggressive and hostile behaviour”, and “Improved mental health in children”, as outlined in the logical framework (Figure 1). The 25 questions are summed to five subscales, ranging from 0 to 10 points (“Emotional problems scale”, “Conduct problems scale”, “Hyperactivity scale”, “Peer problems scale”, and “Prosocial scale” [Range: 10–0 points, with lower scores indicating lower prosocial skills]) and the “Total difficulties score”, ranging from 0 to 40 points, with higher scores indicating more problems. The SDQ showed good internal consistency of the Total Difficulties Score in 1394 Italian children aged 8–10 years [26].

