#### 2.11.3. Quantitative Statistical Methods and Qualitative Data Analysis

A mixed method approach using quantitative and qualitative measures will be used. Quantitative measurements will evaluate potential effectiveness, including a prospective collection of outcome data assessing changes in children’s behaviour, parenting skills, and family adjustment in caregivers. In addition, qualitative interviews will facilitate an understanding of the caregiver’s experience in taking part in the intervention and the cultural acceptability.

We will follow CONSORT guidelines for reporting and quantitative analysis. Statistical analysis will be undertaken by a researcher with relevant expertise and an analysis of quantitative measures will be conducted upon completion of the final measures, three months post-intervention.

All data will be analysed according to the intention to treat. Ideally, all participants will be followed up with, as has previously been performed. In case of a loss of follow-up or not all questions being answered, a non-responder analysis will be performed and those who did not attend a follow-up will be compared to the remaining. Missing data will be excluded from the analyses or imputed using the serial mean, depending on the amount of missing data.

The normality of the data distribution will be assured through a visual inspection of the histograms, Q-Q plots, and box plots. Cronbach’s alpha coefficients will be calculated to assess internal consistency.

For demographic data, continuous variables will be presented as means and standard deviations (SD), with a 2-sample *t*-test for comparison; whereas, categorical data will be summarised as frequencies and proportions and compared using a chi-square test. In case of non-normality, the respective non-parametrical tests will be used.

To compare scores at the different time points, we will conduct a two-way multi-level mixed ANOVA (time: within-subjects factor and group: between-groups factor), considering the subject and the territory random effects. This overall analysis will be followed by the simple effect analysis, if the interaction is significant, and by post hoc tests for the main effect of time, if significant, using use a method based on the false discovery rate (e.g., Holm’s correction), proportional to the size of the difference between the means.

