Regression analyses (SEM) will also be conducted between the parental dimensions and the filial dimensions to evaluate the effect of parental change on the behaviour and emotional state of the child.

Stratified analyses will be conducted by gender, as well as for participants with worse scores (below the 33rd or above the 66th percentile) at baseline. Statistical significance will be set at a *p*-value lower than 0.05.

Qualitative data will be analysed using thematic analysis (TA) [31], where dominant themes will be identified through a close examination of the data. First, open coding will be carried out and an initial coding schedule will be devised in order to define each emerging theme. The coding manual will then be revised throughout the coding of the remaining transcripts. The original codes will frequently be combined or divided into further codes, depending on the emergent findings. Themes will be continually compared with newly coded interview transcripts to ensure that they are readily applicable to the data by using the research team’s familiarity with the text and coding manual to frequently assess and reassess how the codes are being applied to the raw data. The coding manual will be discussed within the research team and amendments will be made if necessary. The team will then develop a revised code set that includes the new and combined codes. NVivo9 software will be used to facilitate the analysis. The analysis will cease when the research team judges that thematic saturation has been reached [31].

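### The primary outcome is the whole questionnaire battery: 17 overlapping scores, no primary score or time point, and no stated correction that reaches across scores

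*Protocol article*

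**What the plan says.** Section 2.5 (Outcomes) states: "The primary outcome of this trial is to assess the efficacy of Family UNited in improving family skills outcomes and family mental health". It then lists parenting skills, parental confidence, caregiver mental health, child behaviour and mental health, resilience and aggression, and says how they are measured: "caregivers and children will complete a battery of questionnaires, right before the intervention (Time 1", and again at Times 2 and 3. The primary objective in section 1.4 is equally broad: "improving family-skills outcomes and caregiver and child mental health and resilience, as reported by caregivers and children". The secondary and tertiary objectives there concern process and acceptability, so no efficacy score is ranked below primary.

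Section 2.11.3 plans a two-way mixed ANOVA (time by group). Simple effects follow if the interaction is significant, and post hoc tests follow a significant main effect of time, "using use a method based on the false discovery rate (e.g., Holm’s correction"). It adds: "Stratified analyses will be conducted by gender, as well as for participants with worse scores". One threshold, p < 0.05, is given for everything.

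On timing, section 2.10 places the follow-ups at "two weeks post-intervention (t2), and six weeks post-intervention (t3"). Section 2.11.3 places the analysis "upon completion of the final measures, three months post-intervention".

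**The concern.** A trial with one primary score tested at 0.05 has a 5% chance of a false positive primary result. Here every efficacy score carries primary status, each is judged at 0.05, and nothing stated links the scores. If one or two of the 17 cross the threshold, the protocol gives a reader no means of telling a real effect from the expected yield of 17 tests. It also leaves open which score and which follow-up will be put forward as the main result.

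The stated correction does not address this. It attaches to comparisons within one score's ANOVA, and most directly to the main effect of time, whereas the treatment effect is the time-by-group interaction.

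**Working it through.** **Count of scores (section 2.10).**
- SDQ: "The 25 questions are summed to five subscales, ranging from 0 to 10 points", plus a total: 5 + 1 = 6
- PAFAS: 4 parenting + 3 family adjustment subscales = 7
- CYRM-R: 2 subscales + overall scale = 3
- ATIPV: 1 total

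Sum: 6 + 7 + 3 + 1 = 17.

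**The plan's own figure, and the alpha behind it.** Section 2.7 gives 40 per group at 80% power. This matches the Parental adjustment row of Table 4 (paired difference 1.2, SD 2.7). With n = ((z for alpha + z for power) × SD / difference)²:
- 80% power: ((1.960 + 0.842) × 2.7 / 1.2)² = 39.7, so 40, as stated.
- 90% power: ((1.960 + 1.282) × 2.7 / 1.2)² = 53.2, so 54, as stated.
- A one-sided 0.05 would give 32, which does not match.

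The sample size therefore assumes a single scale at an unadjusted two-sided 0.05.

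**Chance of at least one false positive.** Assume no effect on any score, one interaction test per score, and each test holding its nominal 5%.
- Expected number of false positives: 17 × 0.05 = 0.85, whatever the correlation.
- Independent tests: 1 − 0.95^17 = 0.582.
- Correlated tests: simulation of 17 equally correlated normal statistics, 400,000 draws, two-sided 1.96.

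| Assumed pairwise correlation | Chance of at least one p < 0.05 |
|---|---|
| 0 (ceiling) | 58% |
| 0.3 | 49% |
| 0.5 | 39% |
| 0.7 | 27% |

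The documents give no correlations, so the range has to be shown.

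**What the remedies cost in power.** This illustration takes Parental adjustment, a between-arm difference in change of 1.2 with SD 2.7, 160 / 2 = 80 families per arm, no clustering and no dropout. The standard error is 2.7 × √(2/80) = 0.427, and 1.2 / 0.427 = 2.81.
- One primary score at 0.05: Φ(2.81 − 1.96) = 80%.
- Two scores, at Holm's first step of 0.025: Φ(2.81 − 2.24) = about 72%.
- All 17 kept as primary with Bonferroni, 0.05 / 17 = 0.0029: Φ(2.81 − 2.97) = about 44%. Restoring 80% would need 148 families per arm.

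**Timing, side by side.** In Table 3 the programme ends in week 7 and Time 3 is week 13, which is 13 − 7 = 6 weeks. This agrees with sections 2.5 and 2.10. Three months (about 13 weeks) after week 7 is about week 20. Only section 2.11.3 gives three months.

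**The case against.** The strongest reply is that this is a condensed article and that multiplicity control is often left to an analysis plan. That stands for the mere absence of a cross-score procedure and of interaction tests for the strata. It does not remove the point, which rests on what the article states: a primary outcome covering the whole battery, one threshold for everything, and a trial sized in section 2.7 to show results on each scale.

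Several stronger readings are tempting, and the documents do not support them.

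- A reader might count both follow-ups and reach 34 tests, with an 83% chance of a false positive (1 − 0.95^34). The written plan has one interaction test per score across all three times, with simple effects only after a significant interaction. Thirty-four free tests are not what it proposes.
- A reader might take 58% as the estimate. The SDQ and CYRM-R totals are built from subscales that are also counted, and one respondent supplies several scores, so independence cannot hold.
- A reader might say the correction covers only post hoc time contrasts. The sentence can also be read to include the simple effects. On either reading it stays within one score.
- A reader might conclude that naming Holm under the false discovery rate leaves error uncontrolled. Holm controls the family-wise error rate, and the false discovery rate never exceeds that, so the named method is the stricter one. The label is a minor misdescription.
- A reader might infer that a three-month measure would compare two treated arms, because Table 3 has control families in the programme in weeks 14 to 17. Section 2.4 lets them start only once all data are collected, so a later Time 3 would delay their start. The inference holds only if the three months are combined with Table 3's calendar and that rule is set aside.
- A reader might say the protocol declares success on any one score. It states no such rule. It states no rule of any kind for combining the scores.

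**Conclusion.** The point holds as an undefined primary endpoint with no stated error control across 17 overlapping scores. Under a global null, the chance of at least one significant primary interaction is about 27% to 49% for assumed correlations of 0.7 to 0.3, which is five to ten times the nominal 5%. The range depends on equal pairwise correlation, one interaction test per score and correct size for each test. The gender and worst-baseline strata would add further tests at the same threshold and are not in these figures.

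This should be settled before outcomes are analysed by arm. The wording about Holm and the three-month phrase are separate, minor corrections and add nothing to the size of the main point.

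**What to change.** By a dated amendment, made before any outcome data are compared by arm:

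1. Name one primary score at one time point, judged on the between-arm (time-by-group) effect at 0.05. Alternatively, name one caregiver and one child score at one time point, with Holm across the two.
2. Make the remaining scores secondary, with one procedure across their between-arm effects: Holm, labelled as family-wise error control, or Benjamini-Hochberg, labelled as false discovery rate control.
3. Label the gender and worst-baseline strata exploratory.
4. In section 2.11.3, stop presenting Holm as a false-discovery-rate method and drop the statement that the correction scales with the difference between means. Holm's thresholds follow the rank of the p-values.
5. Reconcile the three-month final measure in section 2.11.3 with the six-week Time 3 in sections 2.5 and 2.10 and Table 3, and with the waitlist rule in section 2.4.

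Cost: most scores lose primary status. The trial is unblinded (section 2.9) and has started (section 4), so this is a change of outcome and not mere wording. Section 2.12.2 requires it to be communicated to investigators, ethics committees, participants, registries and journals. The choice also has to fit the sample size: 40 matches the Parental adjustment row, while Table 4 lists 45 for Personal resilience and 104 for Total CYRM. A single primary score keeps alpha at 0.05.

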### 2.6. Participant Timeline

Conducting a pilot study before embarking on the RCT ensured that research assistants were confident with the use of the tools with families and that facilitators had the chance to deliver the programme to families (Table 3). Further, in the pilot study, potential difficulties in delivering the training were noted and the modality of programme delivery was optimised (i.e., recruitment of families, timing of the sessions, room, equipment, etc.).

### 2.7. Sample Size

In the pilot study, 26 caregivers (17 in Parma and 9 in Trentino) completed the data collection before the intervention; whereas, only 18 caregivers (11 in Parma and 7 in Trentino) completed the data collection 2 weeks after the intervention. Overall, 19 children (11 in Parma and 8 in Trentino) completed both data collections. Based on the completion of both time points and excluding missing data, the following sample sizes were estimated. To keep the power at 80%, and to be able to show results for each of the scales, the sample size was calculated to be 40 participants in each group, resulting in a total number of families of 160, as shown in Table 4 and Figure 2.

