### 1.5. Trial Design

To explore feasibility and ensure adequate implementation modalities, a pilot study was conducted in March/April 2022.

Subsequently, we plan to conduct a multi-site, non-blinded, 1:1 cluster-randomised controlled trial (cRCT) with two arms used to assess efficacy: the (1) intervention group (receiving the Family United programme) and (2) waitlist/control group (families only receiving the Family UNited programme after the completion of all data collection points).

We will prospectively collect all outcome data, assessing changes in parenting skills and family adjustment in caregivers, children’s behaviour, resilience capacities, and attitudes towards peer violence.

To assess programme delivery, fidelity, feasibility, and acceptability, we aim to include an embedded process evaluation.

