Through the 30-item Parenting and Family Adjustment Scales (PAFAS) we intend to measure potential changes in caregivers related to short-term impacts, such as “Improved caregiver confidence in family management skills”, “Improved caregiving in parenting skills”, and “Increased capacity to cope with stress”, as outlined in the logical framework in Figure 1. The 30 questions are summed into 7 subscales, 4 parenting subscales (“Parental Consistency” [Range: 0–15], “Coercive parenting” [0–15], “Positive encouragement” [0–9], and “Parent-child relationship” [0–15]) and 3 family adjustment subscales (“Parental adjustment” [Range: 0–15], “Family relationships” [0–12], and “Parental teamwork” [0–9]). Higher scores on each of the scales mean worse outcomes; so, a decrease in scores after the intervention would mean a beneficial effect. The PAFAS subscales have shown good internal consistencies in two Australian samples (ranging from 0.70 to 0.87) and satisfactory construct and predictive validity [27].

Children are requested to fill in the 17-item revised Child and Youth Resilience Measure (CYRM-R), through which we aim to measure the short-term impacts, such as “Reduced aggressive and hostile behaviors”, “Increased capacity to cope with stress”, and “Improved mental health outcomes in children”. The CYRM-R comprises 2 subscales, the “Personal resilience subscale”, ranging from 10 to 50 points, and the “Caregiver resilience subscale”, ranging from 7 to 35 points. The overall scale is then summed out of the two subscales and ranges from 17 to 85 points, with higher scores indicating more resilience. The CYRM-R showed good overall fit statistics and a Rasch analysis indicated good psychometric properties for both subscales [28]. In our trial, we will use the 5-point version for youth aged 10–23 years with simplified language.

Children will further fill in the 14-item “Attitude Toward Interpersonal Peer Violence” (ATIPV) measure, with which we aim to measure “Reduced aggressive and hostile behaviors”, “Increased capacity to cope with stress”, and “Improved mental health outcomes in children”. A higher total score (summarised from each question ranging from 1 to 4 points) means a higher level of knowledge and skills in resolving conflicts non-violently. Through this measure, youth are asked to indicate their opinions or feelings about fighting (defined as physical fights, with pushing and hitting), not just arguments [29].

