Week 3–6	Families take part in weekly sessions of Family UNited for 4 weeks
Week 6	All families’ complete measures again (Time 2)
	RCT
Week 1–2	Research Assistants assess families for eligibility and inform them about the planned trial and the programme verbally and in writing
Week 3	Research Assistants recruit 160 families, obtain written assent/consent and conduct baseline measures (Time 1; pre-intervention) with all families After data collection has been completed, families are randomly allocated to intervention or control group
Week 4–7	Intervention group families take part in weekly sessions of Family UNited for 4 weeks Facilitators and observers complete process evaluation tools after each session
Week 9	ALL families complete measures again (Time 2; post-intervention). 10 caregivers from the intervention group are interviewed for acceptability
Week 13	ALL families complete measures again (Time 3; follow-up)
Week 14–17	Control families take part in weekly sessions of Family UNited for 4 weeks

**Table 4 ijerph-20-06548-t004:** Sample size estimates based on selected (statistically significant in paired *t*-test *) results from the pilot trial for Family UNited in Parma and Trentino, Italy, in spring 2022 [25].

	Before: Mean ± SD	After: Mean ± SD	Paired Difference in Means ± SD	Sample Size (Power)	
PAFAS				80%	90%
Positive encouragement (*n* = 14)	5.1 ± 2.3	2,1 ± 1.2	3.0 * ± 2.7	**10**	**12**
Parental adjustment (*n* = 14)	5.9 ± 3.1	4.7 ± 2.7	1.2 ± 2.7	**40**	**54**
Family relationships (*n* = 14)	3.8 ± 2.3	2.9 ± 1.7	0.9 * ± 1.2	**17**	**21**
SDQ					
Hyperactivity (*n* = 14)	2.8 ± 2.1	2.1 ± 1.8	0.7 * ± 1.1	**23**	**30**
Conduct problems (*n* = 14)	2.6 ± 1.8	1.3 ± 1.1	1.4 * ± 1.4	**12**	**15**
Total Difficulty Scale (*n* = 14)	10.9 ± 5.0	8.4 ± 4.4	2.6 * ± 3.7	**20**	**26**
CYRM-R					
Total CYRM (*n* = 12)	58.8 ± 19.0	60.8 ± 18.2	1.9 ± 6.9	**104**	**138**
Personal resilience (*n* = 12)	35.8 ± 11.8	37.4 ± 11.3	1.7 ± 3.9	**45**	**61**

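### Section 2.7 claims 80% power on every scale with 40 per group, but the Table 4 it cites requires 104 for Total CYRM-R

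*Protocol article*

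**What the plan says.** Section 2.7 gives the aim as "To keep the power at 80%, and to be able to show results for each of the scales" and the result as "the sample size was calculated to be 40 participants in each group, resulting in a total number of families of 160", and refers to Table 4 and Figure 2 (the figure is not reproduced in the text at hand).

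Table 4 is captioned "Sample size estimates based on selected (statistically significant in paired *t*-test *) results from the pilot trial". It lists eight scores with the pilot before-after change, its SD, and the sample size for 80% and 90% power. The Total CYRM row ends "1.9 ± 6.9 104 138": change and SD, then the sizes for 80% and 90%. At 80%, Parental adjustment needs 40, Personal resilience 45, and the other five rows between 10 and 23. There is no ATIPV row.

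Section 1.5 describes a "1:1 cluster-randomised controlled trial (cRCT) with two arms". Section 2.11.3 says "Statistical significance will be set at a *p*-value lower than 0.05" and does not state sidedness. Section 2.5 includes children's resilience capacities, aggression and hostile behaviour in the primary outcome. Section 2.10 assigns CYRM-R and ATIPV to measure impacts of this kind.

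**The concern.** The figure of 40 matches the Parental adjustment row, which is not the largest requirement in the table. A sentence promising 80% power on all scales needs the largest, and that is 104.

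At stake is how the child-reported results will be read. Someone relying on Section 2.7 would take a non-significant Total CYRM-R or ATIPV result as coming from an adequately powered comparison. For Total CYRM-R the plan's own table says otherwise, and for ATIPV the table says nothing.

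**Working it through.** **Inputs.** Pilot changes and SDs from Table 4; alpha 0.05 from Section 2.11.3, taken as two-sided because that fits the table.

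**Reproducing Table 4.** For a paired test, the normal approximation is n = (1.960 + 0.842)² × (SD / change)² = 7.849 × (SD / change)². The exact version uses the noncentral t.

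| Row | Normal approximation | Noncentral t | Printed |
|---|---|---|---|
| Parental adjustment | 7.849 × (2.7/1.2)² = 39.7, so 40 | 42 | 40 |
| Total CYRM | 7.849 × (6.9/1.9)² = 103.5, so 104 | 106 | 104 |
| Personal resilience | 7.849 × (3.9/1.7)² = 41.3, so 42 | 44 | 45 |

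The t version comes within 2 of all eight printed 80% figures. Allowing for rounding of the printed inputs, Total CYRM needs 99 to 113 (t version). A one-sided test would still need 83, but one-sided sizes do not fit the table (33 against the printed 40 for Parental adjustment).

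**What 40 per group means.** 2 × 40 = 80, so 160 must be 4 × 40. Two arms by two sites would explain this, although the text does not say so. With 1:1 allocation, 160 / 2 = 80 families per arm. Both readings are carried below.

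**Power by the plan's paired method.** The noncentrality is (change / SD) × √n. For Total CYRM, 1.9/6.9 = 0.275, giving 0.275 × √40 = 1.74 and 0.275 × √80 = 2.46.

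| Row | Power at n = 40 | Power at n = 80 |
|---|---|---|
| Total CYRM | 39.7% | 68.2% |
| Personal resilience | 76.7% | 97.1% |
| Parental adjustment | 78.3% | 97.5% |

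The other five rows have at least 97% at n = 40. With the most favourable rounding of its inputs, Total CYRM reaches 71% at n = 80.

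**Detectable change, paired, SD 6.9, 80% power (normal approximation).** √7.849 × 6.9 / √n = 2.80 × 6.9 / √n, which is about 3.1 points at n = 40 and 2.2 points at n = 80, against the pilot change of 1.9.

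**Secondary: a between-arm comparison.** Assume that the pilot change is the difference between arms (no mean change in controls), that the pilot SD of change holds in both arms, and that there is no clustering and no loss. Then n per arm = 2 × 7.849 × (6.9/1.9)² = 207.02, so 208. Power for Total CYRM-R is 22.9% at 40 per arm and 40.9% at 80 per arm.

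**The case against.** Several points on the other side stand.

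- **Personal resilience is weak evidence.** Its 45 exceeds 40 by little, rounding of the inputs alone allows 40 to 47, and 80 per arm covers it. A reader might infer that child resilience as a whole is badly underpowered. By the paired method that holds for the total score, not for this subscale.
- **Scores without a row are not shown to be unplanned.** The article says "The 30 questions are summed into 7 subscales" for PAFAS and "The 25 questions are summed to five subscales" for SDQ. Adding the SDQ total, three CYRM-R scores and ATIPV gives 7 + 6 + 3 + 1 = 17, against eight rows. A reader might infer that nine scores were never considered. The caption calls the rows selected and cites the pilot report, which may hold further estimates, and the word for scales in Section 2.7 could mean instruments or table rows. What stands is narrower: the cited table gives no support for ATIPV, a whole instrument.
- **Selection on pilot significance did not set the size.** A reader might infer that 40 is too small because it rests on effects chosen for being significant. The row that matches 40, Parental adjustment, has no asterisk and gives p = 0.12 from its printed figures. The article does not offer the smaller sizes as proof of ample power.
- **The between-arm figures are conditional.** The planned analysis is a multi-level mixed ANOVA over three time points, not a two-sample test of change. The 23% and 41% should not be read as the trial's established power.

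One might also say that 160 pairs would suffice for Total CYRM-R (93% paired power). That would count control families as treated, whereas Section 2.4 gives them the programme only after all data are collected.

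None of this removes the conflict between the sentence and the Total CYRM row.

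**Conclusion.** The point holds for Total CYRM-R. Table 4 requires 104 at 80% power, and neither 40 per group nor 80 per arm supplies it; paired power is about 40% and 68%. This rests only on the plan's printed figures, its paired method and two-sided alpha 0.05. Table 4 is arithmetically sound, so the fault is a sentence that claims more than its table shows.

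For Personal resilience the shortfall is small under the reading of 40 and absent under 80 per arm. For ATIPV the claim is unsupported by the table, not shown to be false. The need for about 208 per arm is a secondary result under the assumptions listed with it. It also means that 104 should not be adopted as a corrected per-arm size.

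**What to change.** In Section 2.7, delete the part of the sentence that extends the power claim to every scale. Name the scores for which the 160 families are sized, and say whether 40 refers to an arm, or to an arm within a site. For Total CYRM-R, and for any other score not covered, state the achieved power or the detectable difference, with the comparison and assumptions behind it. State that Total CYRM-R and ATIPV results will be read as estimates with confidence intervals, so that non-significance is not taken as absence of effect.

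The cost is wording only. Recruitment and design are unchanged, so it remains feasible although Section 4 reports that the trial has started. The price is a less favourable stated claim.
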